**Fig. 2 Fig2:**
[figure not shown]
Schedule of enrolment, interventions, and assessments. Abbreviations: CROM, cervical range of motion; HILT, high-intensity laser therapy; MPI, pain intensity at movement; ND, neck disability; PPT, pain pressure threshold; ROM, range of motion; RPI, pain intensity at rest; t1, post-treatment evaluation; t2, follow-up evaluation; W, week

#### Pressure pain threshold (PPT)

The evaluation of the PPT will be carried out through pressure algometry. The procedure will be performed with the participant in the prone position with the arms at the side of the trunk. For the study, the digital pressure algometer FPX (Wagner) will be used. Six points of the cervical spine and shoulder region will be evaluated according to the protocol of Rampazo et al. (Fig. 3) [24]: 2 cm lateral to the spinous processes of C2, C5, T4, and T8, midpoint of the upper trapezius muscle (between the spinous process of C7 and the acromion) and levator scapula muscle (2 cm superior to the superior angle of the scapula). Kilograms of pressure per square centimeter of surface (kg/cm^2^) will be recorded. The measurements will be carried out three times for each point with an interval of 30 s, and the mean value will be recorded as the pressure pain threshold (PPT). The kg/cm^2^ of pressure at which the participant reported pain with the test will be recorded in a Microsoft Excel® spreadsheet [24, 37, 38].

**Fig. 3 Fig3:**
[figure not shown]
PPT recording points

Intra-rater reliability for the PPT measurement will be determined with the intra-class coefficient after assessing the PPT of the midpoint of the upper trapezius muscle belly in 13 healthy volunteers not involved in the study with a 48-h interval between assessments [39].

#### Pain intensity at rest and on movement (RPI and MPI)

Pain intensity will be evaluated through the numerical pain scale (NPRS: intra-rater reliability; intraclass correlation coefficient, ICC = 0.76 (95% CI: 0.51,0.87) [29]. The RPI will equal the magnitude of neck pain reported by the participants at rest, while the MPI will be represented as the magnitude of pain reported by the participants when performing active cervical movements in the sagittal (flexion–extension), coronal (neck right and left side bending), and transverse planes (right and left rotation) [31]. The paint intensity with NPRS will be assessed for each movement using a single attempt (a total of six movements). The RPI and MPI exams will be performed by the participant in a seated position, keeping the back straight and supported on a backrest. The RPI and MPI values will be recorded on a Microsoft Excel® spreadsheet.

#### Cervical range of motion (CFROM) — CROM device

The CROM will be equivalent to the range of active movement of the head with respect to the trunk in the movements of flexion, extension, right and left side bending, and left and right rotation [32–34]. The ranges of movement will be evaluated through an inclinometer (CROM device), registering the degrees of movement for the described movements (inter-rater reliability: ICC extension = 0.98 (95% CI 0.95, 0.99); ICC flexion = 0.89 (95% CI 0.73,0.96); ICC left rotation = 0.95 (95% CI 0.87, 0.98); and ICC right rotation = 0.92)) [32–34]. The CROM values for each movement will be recorded. Three active CROM attempts will be made (30 s between each attempt), recording the best value for each movement.*Cervical flexion and extension (sagittal plane)*: The participant will be sitting with a straight back to stabilize the thoracic spine. The physical therapist will place the inclinometer in the sagittal plane over the upper aspect of the head (midline), stretching the skin of the skull to decrease movement of the skin during the measurement, while using the other arm to help stabilize her trunk. The inclinometer will place at 0 to subsequently request maximum flexion and extension movements.*Cervical side bending assessment (coronal plane)*: The participant will be sitting with a straight back to stabilize the thoracic spine or the wall to the side to stabilize the trunk. The therapist places the inclinometer on the head in the frontal plane, spreading the skin on the scalp as described above. The inclinometer will be set to zero, and the participant will be asked to tilt their neck to one side while the angle is recorded. The procedure is then repeated on the other side.*Cervical rotation (horizontal plane)*: The participant will be placed in the supine position. The physiotherapist will place the inclinometer on the model’s forehead and set the inclinometer to 0. The participant is then asked to rotate the head maximally to the right, and the measurement is recorded. The same process was repeated to measure the rotation to the left.

#### The Neck Disability Index

Neck disability will be considered any partial or total limitation of the functionality of the cervical region due to pain that makes the normal development of the person’s activities of daily living impossible or difficult. Neck disability will be assessed through the Neck Disability Index (NDI), which consists of 10 sections with questions related to symptoms and activities of life that may be limited by NP and has been validated in Spanish [35]. Each section consists of questions scored from 0 to 5, with greater disability being associated with a higher score (NDI, inter-rater reliability: ICC = 0.93 (95% CI 0.86, 0.97) [35, 36]. The neck disabilities percentages will be recorded.

### Participant timeline {13}

Figure 4 displays the participant timeline.

**Fig. 4 Fig4:**
[figure not shown]
Flowchart of the randomized clinical trial

### Sample size {14}

The sample size was determined with the G-Power program using a power of 0.80 (1-*β*), a reliability of 95%, an error of 5% (*α*), and an effect size of *d* = 0.6 (Cohen’s *d*) with reference to previous studies that determined differences in mean pain intensity between experimental and control groups after HILT treatment with effect sizes of 0.53 [30, 40]. Based on the above, the calculated sample size is 72 subjects, with at least 36 subjects per group. The study will include 84 participants (42 per group) in recognition of the crucial role of sample size in determining the power and impact of the study. An additional 15% of participants were considered for possible losses during the follow-up (bias due to abandonment). This is consistent with what the literature recommends, which suggests including at least 10% more participants, and with the PEDro scale (criterion 8), which advocates for analyzing at least 85% of the data to maintain data validity and obtain more robust statistical results and analysis [41, 42].

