### Objectives {7}

The main purpose of the research is to investigate whether pain intensity will decrease after HILT treatment compared with sham HILT after treatment and with a 3-month follow-up. Additionally, secondary outcomes such as changes in pain pressure threshold, active cervical range of motion (flexion, extension, left- and right-side bending, and left and right rotation), and cervical disability will be evaluated. The hypothesis of the study is that HILT will lead to greater pain intensity improvement than conventional treatment. The purpose of this article is to describe the methods and statistical analysis of this study so that this information can be made public.

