## Statistical methods

### Statistical methods for primary and secondary outcomes {20a}

The descriptive statistics for the variables RPI, MPI, PPT, CROM, and ND will be used as analysis measures: averages and standard deviation (*x*, SD), median and interquartile range (mean, IQR), depending on the distribution of the data (test of Kolmogorov–Smirnov normality). From these data, a table will be constructed with the demographic data of the participants by group. The secondary variables sex and body mass index (BMI) will be presented with frequencies and averages or medians, respectively, according to the analysis of the normality of the data. For the inferential statistical analysis of the outcome measures, the Kolmogorov–Smirnov normality test and the Bartlet test will be used to determine the distribution of the variables PPT, RPI, MPI, CROM, and ND, and the corresponding homoscedasticity of the variances obtained for these variables in the evaluations (T0, T1, and T2). According to the results, parametric or non-parametric tests will be selected: the changes in the measurement variables within and between groups will be analyzed with the two-factor ANOVA or the Kruskal–Wallis test, depending on the distribution of the data. Subsequently, a post hoc analysis will be carried out with the Tukey or Bonferroni test, depending on the statistical differences. The significance level for all statistical tests will be set at 0.05. Data will be analyzed using IBM Statistical Package for the Social Sciences (SPSS) software (version 26; SPSS Inc.; Chicago, IL) by an investigator who is blind to group assignment.

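### The 72 participants for 80% power are reproduced from the stated inputs only by a one-sided t-test; a two-sided two-sample comparison at that size has about 71% power.

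*Protocol article*

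**What the plan says.** **Sample size {14}.** The calculation is described as follows: "The sample size was determined with the G-Power program using a power of 0.80", with "a reliability of 95%, an error of 5" per cent (alpha) and "an effect size of *d* = 0.6". The effect is set by reference to earlier studies of "differences in mean pain intensity between experimental and control groups after HILT treatment with effect sizes of 0.53 [30, 40". The result is "Based on the above, the calculated sample size is 72 subjects, with at least 36 subjects per group". Enrolment is then raised to 84 (42 per group) to allow 15% for losses. The section names the software but not the test or the number of tails.

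**Statistical methods for primary and secondary outcomes {20a}.** Changes within and between groups "will be analyzed with the two-factor ANOVA or the Kruskal–Wallis test, depending on the distribution of the data", followed by Tukey or Bonferroni post hoc tests. "The significance level for all statistical tests will be set at 0.05".

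**Objectives {7}.** "The hypothesis of the study is that HILT will lead to greater pain intensity improvement than conventional treatment". This gives a direction of interest. Trial design {8} calls the trial a superiority trial. Neither section sets a one-sided rejection rule.

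**The concern.** Cohen's d is the effect-size input of a two-sample t-test. With d = 0.6, alpha 0.05 and power 0.80, a two-sided t-test needs clearly more than 36 per group, so the stated 72 appears to come from a one-sided calculation. The tests named for the analysis are non-directional at 0.05, which for two groups amounts to a two-sided test. If so, the 80% was calculated for an easier test than the one planned.

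The effect used is also larger than the effect cited in its support, and no reason is given.

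What is at stake is how a null result is read. A trial described as having 80% power invites the conclusion that an effect of d = 0.6 has been made unlikely. If the chance of missing such an effect is nearer 29% than 20%, that conclusion is weaker than it looks.

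**Working it through.** **Inputs.** d = 0.6, alpha = 0.05, power = 0.80, 36 per group, 84 enrolled, 15% loss and cited effect 0.53 all come from Sample size {14}. The non-directional tests at 0.05 come from Statistical methods {20a}.

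**Formula.** For n per group in a two-sample t-test, the noncentrality is δ = d × √(n/2) on 2n − 2 degrees of freedom. One-sided power is P(T > t₀.₉₅). Two-sided power is P(|T| > t₀.₉₇₅). T is noncentral t with noncentrality δ.

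**Step 1: reproduce the plan's figure.** At d = 0.6 and n = 36, δ = 0.6 × √18 = 2.546 on 70 df.
- One-sided critical value 1.667: power 0.8095. At n = 35, power is 0.7996, just short of 0.80. The smallest n is therefore 36 per group, 72 in total, an exact match.
- Two-sided critical value 1.994: power 0.709. The smallest n for 80% is 45 per group (0.804; n = 44 gives 0.795), 90 in total.

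**Step 2: try other routes to 72.**
- One-way ANOVA on two groups with f = d/2 = 0.3 gives 90.
- A one-sided Mann–Whitney test gives about 38 per group.
- A repeated-measures between-group ANOVA gives 72 with f = 0.3, three measurements and a correlation of 0.7, but the section states none of these.

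Among standard calculations using only the stated inputs, the one-sided t-test is the only match.

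**Step 3: two-sided power at the protocol's group sizes.**

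| n per group | d = 0.6 | d = 0.53 |
|---|---|---|
| 36 (calculated) | 0.709 | 0.602 |
| 40 (Sequence generation {16a}) | 0.755 | 0.648 |
| 42 (all 84 analysed) | 0.776 | 0.670 |
| Needed for 80% | 45 (90 total) | 57 (114 total) |

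The reserve does not close the gap, because it is there for losses: 84 × 0.85 = 71.4, about the original 72. With 36 per group, two-sided power reaches 80% at d = 0.67.

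**Step 4: the cited effect under one-sided testing.** At d = 0.53 and 36 per group, one-sided power is 0.72. The 80% therefore does not hold at 0.53 under either sidedness.

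**Step 5: dependence on the correlation.** These figures are for 36 per group, two-sided, d = 0.6. The correlation r between repeated measurements is an assumption, since the document gives none. The change-score column uses d/√(2(1 − r)). The group-by-time column takes compound symmetry and the same effect at both post-baseline visits.

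| r | Change from T0 to T1 | Group-by-time F over T0, T1, T2 |
|---|---|---|
| 0.3 | 56% | 59% |
| 0.5 | 71% | 74% |
| 0.6 | 80% | 84% |
| 0.7 | 90% | 93% |

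For a baseline-adjusted comparison the effective size is d/√(1 − r²). At r = 0.5 this is 0.6/0.866 = 0.693, power 83%. For d = 0.53 it is 0.612, power 73%.

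**The case against.** The arithmetic is not in dispute. The objections concern what may be concluded from it.

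- **Sidedness is inferred.** A reader might infer that the protocol declares a one-sided calculation and a two-sided analysis. It uses neither term. The first is deduced from a numerical match, the second from the nature of the named tests. With a directional hypothesis in a superiority trial, one-sided sizing may have been deliberate. This stands. The supportable defect is that sidedness is unstated and the sizing does not match the tests named.
- **71% is not the power of the planned analysis.** A reader might infer that the trial's true power is 71%. That figure belongs to an unadjusted two-sample comparison. The plan is a two-factor ANOVA over T0, T1 and T2, whose power depends on an unstated correlation and could fall on either side of 80%. This also stands. It does not rescue the stated figure, because the calculation as described uses no correlation.
- **0.53 need not be the planning value.** A target difference may exceed an earlier estimate, and the cited studies are not at hand. The 60% is therefore a sensitivity value, not a second arithmetic error. What remains is that the plan gives no reason for preferring 0.6.
- **The shortfall is modest if nobody is lost.** With all 84 analysed, power at d = 0.6 is 78%. True, but the plan itself sets the extra participants aside for losses.

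**Conclusion.** The point holds in a limited form. On the calculation's own terms, 72 participants support 80% power only for a one-sided two-sample t-test. No section declares one, and the named tests are non-directional at 0.05. For a two-sided two-sample comparison at d = 0.6, the shortfall is about 9 percentage points with 36 per group and about 2 with no losses from 84.

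This rests on reading d as a two-sample standardised difference and on treating the F and Kruskal–Wallis tests as two-sided for two groups. The documents do not show that the planned ANOVA is underpowered, nor that it is adequately powered. They lack the correlation needed to say. The statement of power should be corrected because it is wrong as written and cheap to put right.

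**What to change.** Keep the enrolment at 84. In Sample size {14}, name the test and its sidedness, and replace the power statement with wording such as: *With 36 evaluable per group, a two-sided 5% two-sample test has 71% power for d = 0.6 (60% for d = 0.53); the detectable difference at 80% power is d = 0.67.* Add a sentence on why 0.6 was chosen over the cited 0.53.

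If the sponsor wants to claim more power from a baseline-adjusted primary analysis, the section should state the assumed correlation between baseline and end-of-treatment pain and show a range. As an example, r = 0.5 would give about 83% at d = 0.6 and 73% at d = 0.53. If one-sided testing was intended, it should be declared and justified, and the analysis section brought into line with it.

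The cost is a rewording of one section. No extra participants are needed. The downside is that the stated power becomes less favourable.

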### Recruitment {15}

The study’s dissemination will take place through Andrés Bello University’s official channels (mailing and publication on the institutional website). Additionally, the Physical Therapy’s School communication channels will be utilized (through mailings, social networks, and posters). Volunteers will be contacted by phone or email to attend the research lab.

## Assignment of interventions: allocation

### Sequence generation {16a}

The selected participants will be allocated into two groups, group 1 (HILT) and group 2 (sham HILT), using a simple randomization process via the website research randomizer [25]. A block randomization with a 1:1:1:1 allocation will be performed, and participants will be stratified by sex, resulting in four subgroups with equal numbers of women and men per group (*n* = 40 per group, 20 men, and 20 women). Each participant will have an equal probability of being randomly allocated to either group 1 or group 2.

### Concealment mechanism {16b}

After the website generates a numerical sequence (https://www.randomizer.org), a concealed allocation will be performed in consecutively numbered opaque envelopes. The envelopes will be sealed, and they will be stored in a secure cabinet. Sample randomization and concealed allocation will be carried out by the principal researcher. The researcher in charge of administering the treatments will open the envelopes just prior to the intervention.

### Implementation {16c}

Four independent physical therapists will work on this study, and each of them will have a specific role. The principal researcher (R1) will oversee participant recruitment, participant registration, randomization, and the random allocation sequence. Moreover, the interventions will be implemented by a researcher (R2) (HILT, sham HILT, and exercise). All evaluations will be performed by a third researcher (R3) (RPI, MPI, PPT, CROM, and ND). The principal researcher will examine and record the data.

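### The principal researcher, who oversees recruitment and registration, also carries out randomization and can know upcoming allocations; the sequence is described in two incompatible ways and for 80 people instead of 84

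*Protocol article*

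**What the plan says.** **Roles.** Implementation {16c}: "The principal researcher (R1) will oversee participant recruitment, participant registration, randomization, and the random allocation sequence". Concealment mechanism {16b}: "Sample randomization and concealed allocation will be carried out by the principal researcher". The envelopes are opaque and consecutively numbered. On their custody the text says only "The envelopes will be sealed, and they will be stored in a secure cabinet"; no custodian is named. The researcher who gives the treatments opens each envelope just before the intervention. Under Eligibility criteria {10} and the consent section {26a}, evaluators check eligibility and explain consent.

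**Method.** Sequence generation {16a} says participants are allocated "using a simple randomization process via the website research randomizer". Its next sentence says "A block randomization with a 1:1:1:1 allocation will be performed", with stratification by sex and equal numbers of women and men in each group. Intervention description {11a} again calls the process simple, with stratification by sex.

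**Number.** Sequence generation {16a} gives "40 per group, 20 men, and 20 women". Sample size {14} says "The study will include 84 participants (42 per group"), reached from 72 by adding 15% for losses.

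**The concern.** Concealment works when the people who bring participants into the trial cannot know the next allocation. An opaque envelope protects against someone who has not seen the list. It does not protect against the person who made it. If that person also oversees recruitment and registration, the order or timing of entry can be influenced, even unintentionally, by the arm that comes next. No later analysis can reliably undo the resulting selection bias.

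The description of the sequence raises a second, more ordinary problem. Simple and block randomization are different procedures, and two people working from this text could build different lists. A four-way ratio lists sex as though it were assigned, whereas sex is a stratum and assignment within it is 1:1. A list of 80 also does not cover the planned enrolment of 84.

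**Working it through.** **Roles, side by side**

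| Task | Who | Section |
|---|---|---|
| Recruitment and registration (oversight) | Principal researcher | {16c} |
| Randomization and sequence | Principal researcher | {16b}, {16c} |
| Carrying out concealed allocation | Principal researcher | {16b} |
| Eligibility check, consent explanation | Evaluators | {10}, {26a} |
| Opening envelopes | Treating researcher | {16b} |
| Custody of the cabinet | Not stated | {16b} |

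The first three rows fall to one person, which is enough for foreknowledge whoever keeps the cabinet.

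**The plan's own sample size**

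- Inputs from Sample size {14}: d = 0.6, α = 0.05, power 0.80, 15% losses. Whether the test is one- or two-sided is not stated.
- A two-sample t-test, one-sided, needs 35.04 per group, so 36 per group and 72 in total. This matches the plan. Two-sided, it needs 44.59, so 45 per group, which does not match 72.
- Adding 15%: 36 × 1.15 = 41.4, so 42 per group and 84 in total. This also matches.

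**The list against the enrolment**

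- List: 2 × 40 = 80. Plan: 2 × 42 = 84. The list is 4 short, and 4/84 = 4.8%.
- For comparison, 36/0.90 = 40, so 40 per group is what a 10% loss allowance would give. The article does not say that this is where the figure comes from.
- After 15% loss: 80 × 0.85 = 68 (34 per group); 84 × 0.85 = 71.4.
- Power at d = 0.6, like for like:

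| Per group | One-sided | Two-sided |
|---|---|---|
| 36 | 0.809 | 0.709 |
| 34 | 0.789 | 0.684 |
| Difference | 0.020 | 0.025 |

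**Can simple randomization give the promised equal cells?**

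With n people in a sex stratum and a fair coin for each, P(exactly equal) = C(n, n/2)/2^n.

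- n = 42 (84 in total, half of each sex): C(42, 21)/2^42 = 0.122. Both strata: 0.122² = 0.015.
- n = 40 (80 in total): both strata 20/20 has probability 0.016.
- A split of 25/17 or worse in one stratum of 42: 2 × P(Bin(42, 0.5) ≤ 17) = 0.28.

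Exactly equal cells in both sexes would thus arise about 1.5% of the time. Only a restricted scheme delivers them by design.

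**The case against.** The strongest reply is that the article contains real safeguards. The principal researcher oversees recruitment, but evaluators, who are blinded to the randomization, decide eligibility and explain consent. The envelopes are opaque, numbered and sealed, and the treating researcher opens them. This stands as mitigation. A reader might infer that the envelopes conceal nothing, or that the principal researcher keeps them; the text supports neither. What remains is that the person who knows the sequence also oversees who is registered.

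A second reply is that block allocation, sex strata and equal cells together show that restricted randomization was meant. That is the likelier intention, and the imbalance figures apply only if the word simple governs. Even then, two 25/17 splits in the same direction (50/34 overall) would lower two-sided power only from 0.776 at 42/42 to 0.760. The text still cannot be followed as it stands.

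Two stronger readings should be resisted.

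- A reader might set the two-sided power of 0.684 at 34 per group against the planned 0.80 and blame the short list. Most of that gap is the unstated sidedness, since 36 per group already gives only 0.709 two-sided. The full 84 less 15% leaves 71.4, itself just under 72.
- A reader might see a conflict between the principal researcher examining the data and an analysis done "by an investigator who is blind to group assignment". No section gives the principal researcher the inferential analysis, and examining and recording data fits the data-management role in {19}. This is not a contradiction.

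**Conclusion.** The point holds in two parts of different weight.

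The substantive part is the overlap of roles. It rests on the plain wording of {16b} and {16c}, and on the assumption that whoever carries out the randomization sees the list. It makes foreknowledge possible; it does not show that allocation would be subverted. The possible bias cannot be sized from the document. Because it could not be repaired in analysis, the overlap should be removed.

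The other part is inconsistent text: simple against block, a four-way ratio for a two-arm trial with two strata, and 80 against 84. These contradictions are certain, but their numerical effect is small. The four missing places cost about 2 points of power one-sided or 2.5 two-sided, assuming 15% loss and d = 0.6. The probability of about 1.5% assumes 42 people of each sex and shows only that simple randomization and equal cells cannot both be promised.

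**What to change.** 1. Rewrite Sequence generation {16a} with one method: separate lists for men and women, 1:1 permuted blocks of varying size within each, 84 places in total. If equal numbers of each sex are kept as the target, that is 42 per list, or 21 per arm within each sex. Delete the word simple (also in Intervention description {11a}), the 1:1:1:1 ratio and the 40 per group.
2. Have the list generated and the envelopes prepared by someone who does not recruit, evaluate or treat, for example a university colleague outside the trial. Name who keeps the cabinet. Keep the principal researcher from the list until database lock.
3. Do not simply pass the task to another of the four therapists. Implementation {16c} appears to leave the fourth without a task, but Outcomes {12} names two evaluators, so the fourth may be the second evaluator, who must stay blinded under {17a}. The treating researcher (R2) applies the allocations and is called an evaluator in {18b}.
4. If participants have already been randomized, state which method was actually used, for how many places, and who had seen the list.

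The cost is one corrected paragraph, a matching word in {11a}, and a one-off task for one person outside the team. Visits, measurements and the planned enrolment of 84 do not change.
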